### Measurements

Measurements will be performed by an independent investigator. Standard measurement will take place preoperatively, and six weeks, three months and one year postoperatively. As it is hypothesised that the anterior approach is superior to the posterolateral approach in terms of a faster recovery, mainly in the early recovery period (shorter hospital stay, faster return to normal ADL functioning), extra measurements of physical function, gait analysis and economic evaluation will take place two weeks postoperatively. The questionnaire will be sent to the patients a few days prior to the visit or – when patient do not have an email – will be filled in during the clinical outpatient visit. The filling in of the questionnaire will approximately take 30 to 45 min of patients’ time. A CONSORT flow chart is provided in Fig. 1. Demographic data, preoperative diagnosis, height, weight and Body Mass Index (BMI), ASA classification and the Kellgren and Lawrence (KL) score will be recorded preoperatively.

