The EuroQol questionnaire (EQ-5D) will also be administered. The health outcomes of the two approaches for THA will be assessed in terms of quality adjusted life years (QALYs). This reflects any differences in health-related quality of life based on the patients’ responses to the EQ-5D questionnaire preoperatively and at up to three points after hospital discharge (six weeks, three months and one year postoperatively). The EQ-5D is a generic questionnaire and consists of 5 questions regarding health-related quality of life [34]. The EQ-5D will also be used as a preference-based measure of health status for the cost-effectiveness analysis [35].

Next to the previous mentioned questionnaires the global rating of change will be assessed [36]. A global rating of change is a single item with which the overall (global) perceived improvement in physical functioning following THA can be assessed. This question is scored on a 7-point likert scale (1 = completely recovered; 2 = much improved; 3 = slightly improved; 4 = not changed; 5 = slightly deteriorated; 6 = much deteriorated; 7 = worse than ever), and asks for the change in physical functioning following THA.

The International Consultation of Incontinence Questionnaire-Short Form (ICIQ-SF) will be administered to evaluate whether THA has influence on urine incontinence [37]. The ICIQ-SF is a subjective questionnaire and is a recommended method to assess the grade of urine incontinence [38]. It consists of four questions on the frequency and volume of urine incontinence and its influence on daily life [37]. With the posterolateral approach the short external rotators of the hip are detached of the greater trochanter. Since the obturator internus muscle is connected to the pelvic floor musculature detachment of this muscle may have a negative effect to urine continence [39, 40], whereas with the anterior approach the pelvic floor remains undisturbed.

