### Statistical analysis

To analyse the data SPSS (Statistical Package for the Social Sciences, Chicago, Illinois) will be used. A *p*-value of < .05 will be considered to indicate statistical significance. Descriptive statistics (means and standard deviations) will be used to describe the subject characteristics and the results of the groups. The PASS score is determined by assessing the score on the HOOS of patients who are satisfied with their actual physical state and symptoms. PASS scores will be determined for the measurements made at six weeks, three months and one year postoperatively. The satisfaction question, which is asked on a four-response Likert scale, will be dichotomized into “satisfied” (i.e. the patients who are “very satisfied” or “somewhat satisfied”) and “unsatisfied” (i.e. the patients who are “somewhat dissatisfied” or “very dissatisfied”) [30, 32]. This dichotomized variable will then be used as anchor to calculate cut-off values on the HOOS to determine the PASS score. Next, a ROC analysis will be conducted, using the satisified/dissatisfied variable as anchor. As optimal cut-off value will be the one that maximizes the sum of sensitivity and specificity [30].

After that, all patients will be categorized as responders (i.e. a score on the HOOS beyond the PASS score) and non-responders. Chi-square tests will be used to determine potential differences in the proportion of responders between the study and control group at the above-stated time-points. Additionally, odds ratios with corresponding 95% confidence interval (CI) will be calculated. This ratio represents the odds of being a “responder” for the study group, compared to the control group. An odds ratio larger than 1 favours the study group and the point estimate of the odds ratio is considered to be statistically significant if the 95% CI does not include the value of 1.

Changes in physical activity, participation and gait function will be analyzed with Generalized Estimating Equations (GEE) analyses [51]. Analysis of Variance (ANOVA) will be used to assess differences in urine incontinence (ICIQ-SF), radiographic measurements, surgical time, blood loss and length of hospital stay between the study and control group. Differences in complication rates will be assessed by means of a Chi-square test.

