For both the study and control group the mean costs, mean effects (measured with HOOS) and mean QALY (based on the utility scores of the EQ-5D) will be calculated. Next, mean costs, mean effects and mean QALYs are used to calculate the incremental costeffectiveness ratio (ICER) [52] by dividing the difference in costs by the difference in effects/QALYs between the study and control group. Uncertainty surrounding the calculated ICER will be examined by the bootstrap method. Incremental cost-effectiveness ratios will be calculated for each of the bootstrap iterations (5000 in the present study), which then will be combined to form a mean ICER with corresponding 95% CI.

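### QALYs and the HOOS effect in the ICER, and ICIQ-SF under ANOVA, are compared without stated baseline adjustment, which costs precision and leaves chance imbalance uncorrected

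*Protocol article*

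**What the plan says.** All places are in the protocol article.

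- **ICIQ-SF, purpose.** Under Physical functioning and health-related quality of life, the questionnaire "will be administered to evaluate whether THA has influence on urine incontinence".
- **ICIQ-SF, analysis.** Under Statistical analysis: "Analysis of Variance (ANOVA) will be used to assess differences in urine incontinence (ICIQ-SF"), in one list with the radiographs, surgical time, blood loss and length of stay. No covariate, change score or analysis time point is named. The preceding sentence assigns changes in physical activity, participation and gait function to GEE; ICIQ-SF is not in that list.
- **Schedule.** Under Measurements: "Standard measurement will take place preoperatively, and six weeks, three months and one year postoperatively". No separate schedule is given for ICIQ-SF.
- **EQ-5D.** QALYs rest on "responses to the EQ-5D questionnaire preoperatively and at up to three points after hospital discharge (six weeks, three months and one year postoperatively"), so the preoperative value is one of the inputs.
- **ICER.** Under Statistical analysis, mean costs, mean HOOS effects and "mean QALY (based on the utility scores of the EQ-5D) will be calculated" per arm. The ICER then follows "by dividing the difference in costs by the difference in effects/QALYs between the study and control group". On uncertainty: "Uncertainty surrounding the calculated ICER will be examined by the bootstrap method", with 5000 iterations. No adjustment is mentioned at either step.
- **Randomisation.** Under Study population and recruitment procedure, there are separate allocation sets for cemented and uncemented stems. No other baseline characteristic is balanced by design.

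**The concern.** ICIQ-SF is meant to show an influence of surgery on continence, and a patient's later score can be expected to depend on the score before surgery. Yet it is grouped with outcomes such as surgical time and length of stay, which have no preoperative counterpart. The QALY contrast has the same weakness: later utility tends to follow preoperative utility, so part of the spread between patients, and part of any chance difference between arms, has nothing to do with the surgical approach.

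Two things are at stake. The confidence intervals are wider than the collected data require. And in the one randomisation that is actually carried out, an imbalance in preoperative incontinence or utility is left in the estimate. For QALYs that estimate is the denominator of the ICER, and cost-effectiveness is part of the trial's stated aim.

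**Working it through.** **Plan's own figures.** The plan gives no figure for ICIQ-SF or QALYs. Its sample size concerns PASS only: 70% against 90%, power 80%, alpha 5% (taken as two-sided), 60 per subgroup. The unpooled formula gives (1.960 + 0.842)² × (0.7 × 0.3 + 0.9 × 0.1) / 0.2² = 58.9, so 59; the pooled version gives 62. Both agree well with 60. Only the number evaluable is used below: 260 × 0.90 = 234, or 117 per arm.

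**Assumptions (not in the documents).** Baseline-to-follow-up correlation r = 0.3, 0.5 or 0.7; equal SDs over time; QALY SD 0.15; correlation of the QALY with preoperative utility 0.3 to 0.5; QALY computed by the trapezoid rule.

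**Step 1: size of chance imbalance.** The SE of a baseline difference, in SD units, is √(2/117) = 0.131. The 95% range is ±1.96 × 0.131 = ±0.26 SD.

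**Step 2: precision.** Relative to unadjusted ANOVA on follow-up scores, the variance ratio is 1 − r² for ANCOVA and 2(1 − r) for ANOVA on change scores.

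| r | ANCOVA ratio | Variance saved | Equivalent extra patients, 1/(1 − r²) − 1 | Change-score ratio |
|---|---|---|---|---|
| 0.3 | 0.91 | 9% | 10% | 1.40 |
| 0.5 | 0.75 | 25% | 33% | 1.00 |
| 0.7 | 0.51 | 49% | 96% | 0.60 |

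In SD units the SE of the ICIQ-SF difference is 0.131 unadjusted and 0.125 / 0.113 / 0.093 with ANCOVA. A change score is worse than plain ANOVA below r = 0.5 and less precise than ANCOVA at each r shown.

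**Step 3: carry-over of an imbalance, ICIQ-SF.** The shift is r × imbalance. For an imbalance of 0.2 SD it is 0.06 / 0.10 / 0.14 SD. With no true effect and an imbalance d = 0.26 SD, put m = r × d / 0.131. The chance of a significant result is 1 − Φ((1.96 − m)/√(1 − r²)) + Φ((−1.96 − m)/√(1 − r²)), about 8% / 13% / 21%. Averaged over all randomisations it is 5%.

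**Step 4: QALY shift.** The SE of the unadjusted difference is 0.15 × 0.1307 = 0.0196. For a one-SE baseline imbalance the shift is correlation × 0.0196:

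- 0.3 × 0.0196 = 0.0059, which is 0.3 of an SE
- 0.5 × 0.0196 = 0.0098, which is 0.5 of an SE

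A two-SE imbalance doubles these to 0.012 to 0.020. Adjustment would reduce the SE from 0.0196 to 0.0196 × √0.91 = 0.0187 or 0.0196 × √0.75 = 0.0170.

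**Step 5: does having baseline in the QALY already adjust for it?** With measurements at 0, 6/52, 0.25 and 1 year, the trapezoid weight of the preoperative utility is (6/52)/2 = 0.058. The slope of the QALY on preoperative utility is 0.058 + 0.942r = 0.34 / 0.53 / 0.72 for r = 0.3 / 0.5 / 0.7, now read as the correlation between preoperative and later utility. An illustrative utility imbalance of 0.05 therefore adds 0.017 / 0.026 / 0.036 QALY. Most of this comes through the later utilities. Including the baseline in the area under the curve does not remove the imbalance; it adds a little to it.

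**The case against.** The strongest reply is that nothing here is invalid. Allocation is random, so the unadjusted differences are unbiased and the type I error is 5% over randomisations. The standard errors and the bootstrap interval already include chance imbalance as part of sampling variation. At a QALY-to-baseline correlation of 0.3 to 0.5 the SE falls by only 5% to 13% (1 − √0.91 and 1 − √0.75). All of this stands, and it makes the point one of efficiency and of error given the imbalance actually observed.

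The ICIQ-SF part also rests partly on inference. A preoperative score follows from the general schedule, not from a statement about that questionnaire, and the schedule does not fit every instrument: the Participation section lists only postoperative visits for the WHODAS II. ANOVA could also mean an analysis of change or of repeated measures. That uncertainty stands. A change-score analysis would still be less precise than ANCOVA, so the advice is the same.

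Covariates might be set out in a full protocol or SAP that is not shown. But the article does not leave the method open. It names ANOVA for one outcome and a difference in arm means for the other, and a better method is available from data already planned.

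Three stronger readings are tempting and are not supported:

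- **That preoperative EQ-5D is ignored.** It is an input to the QALY; what is missing is adjustment for it.
- **That imbalance passes in full into the results.** For ICIQ-SF the shift is scaled by r, and for QALYs by the slope in Step 5.
- **That the QALY shift rivals the treatment effect or would reverse the economic conclusion.** The documents give no expected QALY difference and no decision threshold, so neither can be shown.

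**Conclusion.** The point holds as a recommended improvement to secondary analyses. As written, the QALY and HOOS contrasts in the ICER and the ICIQ-SF comparison are valid but inefficient, and they leave any chance baseline imbalance uncorrected. The variance forgone is about 9% to 49% over the assumed range of r, and the low end is modest. A one-SE imbalance moves the QALY difference by 0.3 to 0.5 of its standard error. These sizes depend wholly on assumed correlations and an assumed QALY SD.

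The case is firmer for QALYs, where the preoperative measurement and the unadjusted contrast are both explicit, than for ICIQ-SF. The PASS comparison and its sample size are unaffected.

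**What to change.** 1. **ICIQ-SF.** Replace ANOVA with ANCOVA, or with a longitudinal model over the postoperative visits such as the GEE already planned for other outcomes. Include preoperative ICIQ-SF and stem type as covariates, and confirm that the questionnaire is completed before surgery.
2. **Economic evaluation.** Estimate the incremental QALY by regression on approach, preoperative EQ-5D utility and stem type. Estimate the incremental HOOS effect in the same way with preoperative HOOS. Refit both regressions within each of the 5000 bootstrap samples so that the interval reflects the adjusted estimate.
3. **Timing.** Fix this before outcome data are examined, so that adjustment is not chosen after an imbalance has been seen.

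The cost is a change of analysis wording. No additional patients are needed, and no new data provided that ICIQ-SF follows the general preoperative schedule.

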**Discussion:**

There is some evidence that the anterior approach results in reduced tissue damage and faster recovery in the direct postoperative period, compared to the posterolateral approach. However, there is still a lack of well-designed studies that have confirmed the better outcomes and cost-effectiveness of the anterior approach. Therefore, the purpose of this study is to assess the physical functioning, health related quality of life and the cost-effectiveness of the anterior approach, compared to the conventional posterolateral approach.

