The anterior approach for THA is a minimally invasive, tissue-sparing technique. Conceptually, the anterior approach should cause less tissue damage compared to the conventional posterolateral approach, as intermuscular planes are used without muscle dissection [6]. Moreover, by (partially) dissecting several muscles around the hip, the posterolateral approach is more prone for instability postoperatively. Whereas with the anterior approach, the musculature for pelvic stabilisation remains undisturbed [7]. These muscles also play an important role in gait function. Hence, theoretically, the anterior approach should result in a faster recovery of physical functioning and, thus, a higher health-related quality of life.

Little research has been conducted so far on the implications of MIS THA, and especially the direct anterior approach (DAA) for THA, in elderly patients [8]. The skeletal musculature of elderly patients possesses a higher vulnerability and a reduced regenerative capacity [9]. Additionally, elderly patients are characterized by a higher incidence of postoperative fatty muscle atrophy, which is associated with reduced muscular function [9]. More importantly, patients who underwent THA through a conventional approach had a significantly higher grade of muscle atrophy compared to older patients following MIS THA. Muller et al. [9] concluded that especially older patients seem to benefit from a minimally invasive approach. Whether the previously mentioned results are also applicable for the anterior approach, is still unknown.

The ability to ambulate independently is an important hospital discharge criterion since a proper gait function is crucial to perform several activities of daily living independently. Thus far, there are no studies that compare the cost-effectiveness of the direct anterior approach. Despite this, there is some evidence that accelerated postoperative care can be cost saving [10]. In this respect the anterior approach, because of its muscle sparing character and potentially faster recovery, might not only be a clinically effective but also a cost-effective surgical technique for THA.

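### Quality of life is a stated purpose, yet EQ-5D is read out only as mean QALYs feeding the ICER, with no between-approach EQ-5D estimate and interval stated

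*Protocol article*

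**What the plan says.** **Purpose.** The Discussion paragraph of the abstract says that "the purpose of this study is to assess the physical functioning, health related quality of life and the cost-effectiveness of the anterior approach". The abstract's Methods/design paragraph also lists quality of life among the outcomes assessed by questionnaire. The Background gives the hypothesis: "the anterior approach should result in a faster recovery of physical functioning and, thus, a higher health-related quality of life".

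**Timing of the expected benefit.** Under Measurements, the hypothesis is that "the anterior approach is superior to the posterolateral approach in terms of a faster recovery, mainly in the early recovery period". For that reason "extra measurements of physical function, gait analysis and economic evaluation will take place two weeks postoperatively"; quality of life is not named among these extras.

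**EQ-5D readout.** Under Physical functioning and health-related quality of life: "The health outcomes of the two approaches for THA will be assessed in terms of quality adjusted life years (QALYs"). EQ-5D is scheduled preoperatively and at six weeks, three months and one year. The same paragraph adds: "The EQ-5D will also be used as a preference-based measure of health status for the cost-effectiveness analysis".

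**Analysis.** The Statistical analysis section assigns methods outcome by outcome:
- PASS responders: chi-square, and odds ratio with 95% CI.
- Physical activity, participation and gait: GEE.
- Urinary incontinence, radiographic measurements, surgical time, blood loss and length of stay: ANOVA.
- Complications: chi-square.

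EQ-5D is not in this list. It appears only in the economic paragraph, where "mean effects (measured with HOOS) and mean QALY (based on the utility scores of the EQ-5D) will be calculated" for each group. The difference is the denominator of the ICER, and the 5000 bootstrap iterations yield a mean ICER with a 95% CI.

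**The concern.** Two features combine.

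First, the only stated EQ-5D result is an ingredient of a cost ratio. The interval given for the ICER describes cost per QALY. It mixes uncertainty in costs with uncertainty in QALYs, and it cannot be read as an interval for the difference in quality of life. Followed as written, the trial gives no between-approach EQ-5D estimate with its uncertainty.

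Second, a QALY is an area under the curve over the whole follow-up, while the benefit is expected mainly early. With no EQ-5D listed at two weeks, six weeks is the only early reading, and the QALY gives it little weight.

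At stake is whether the report can say, on the generic scale, if and when the anterior approach changes quality of life. A contrast fixed in advance would also remove any later choice of visit or summary.

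**Working it through.** **The plan's own figure.** The only design calculation concerns PASS: 70% against 90%, 80% power, alpha 5% (two-sided assumed). The unpooled formula gives (1.96 + 0.8416)² × (0.70×0.30 + 0.90×0.10) / 0.20² = 7.849 × 0.30 / 0.04 = 58.9, against the stated 60 per subgroup. It reproduces and is not in dispute. The plan gives no figure for EQ-5D.

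**Weights of the EQ-5D visits in a QALY.** Visits at weeks 0, 6, 13 and 52 come from the EQ-5D schedule. The one-year horizon and the trapezoidal rule are assumptions; the Statistical analysis section states neither. Each visit's weight is half the span between its neighbours, divided by 52:

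| Visit | Calculation | Weight |
|---|---|---|
| Preoperative | (6 − 0)/2/52 | 0.058 |
| Six weeks | (13 − 0)/2/52 | 0.125 |
| Three months | (52 − 6)/2/52 | 0.442 |
| One year | (52 − 13)/2/52 | 0.375 |

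The weights sum to 1. Three months and one year together carry 0.817. The weights need no assumption about utilities or SDs.

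**QALY difference for an assumed 0.10 utility difference at six weeks, none preoperatively or at one year:**
- Gone by three months: 0.125 × 0.10 = 0.0125.
- Half left at three months: 0.0125 + 0.442 × 0.05 = 0.035.
- Fully present at three months: 0.0125 + 0.442 × 0.10 = 0.057.

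**What this could mean for precision.** The documents give no utility difference and no SD, so these inputs are assumed: SD 0.10 to 0.20 for QALYs and 0.20 to 0.25 for EQ-5D at six weeks. The number per arm is 260 × 0.90 / 2 = 117. Two-sided 5% power is Φ(Δ / (SD × √(2/117)) − 1.96) plus the negligible or small opposite tail, with √(2/117) = 0.1307.

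| Comparison | Difference | Power |
|---|---|---|
| EQ-5D at six weeks | 0.10 | 86% to 97% |
| QALY, gone by three months | 0.0125 | 8% to 16% |
| QALY, half left at three months | 0.035 | 26% to 75% |
| QALY, fully present at three months | 0.057 | 58% to 99% |

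Persistence to three months, more than effect size or SD, drives the loss. The article states neither of these two tests, so the table only illustrates the sensitivity of each summary.

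**The case against.** **An article may leave this to an analysis plan.** The article does not call its list of methods exhaustive, and it plans means and SDs for the results of the groups, which could include EQ-5D. This stands in part: nothing forbids an EQ-5D comparison. But the article does more than stay silent. It names QALYs as the way the health outcomes will be assessed, and it assigns methods by outcome down to urinary incontinence. Group means and SDs are not an estimate of the difference with an interval.

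**QALYs are a declared and legitimate summary.** True, and they belong in the economic evaluation. The point is that their difference is given no interval of its own and that they weight early visits lightly.

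**A reader might infer that the trial can say nothing about quality of life.** The documents do not support that. The HOOS has a hip-related quality-of-life subscale, and HOOS-based PASS is compared between approaches with odds ratios and 95% CIs at six weeks, three months and one year. The gap is in the generic measure.

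**A reader might infer that the QALY result would look null.** That holds only if the difference has vanished by three months. The Sample size calculation hypothesises a 20-point PASS difference at three months, where the QALY weight is 0.442.

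**The main-text aims** speak of clinical and cost-effectiveness; quality of life as a separate purpose stands in the abstract and as a hypothesis in the Background. This limits the weight of the point without removing it. A reader might also extend it to the global rating of change, but the lack of a named test there is ordinary missing detail.

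**Conclusion.** The point holds for EQ-5D. A stated purpose is read out on the generic scale only through mean QALYs in the ICER, with uncertainty stated for the ICER alone; no contrast by visit and no interval for the QALY difference is stated.

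The firm part of the size is the weighting: given a one-year horizon and trapezoidal QALYs, a difference confined to six weeks is diluted eightfold, while one that lasts to three months is diluted much less. The power figures rest wholly on assumed utilities and SDs and support no general forecast of the QALY result. This is a weakness in a secondary analysis; the primary PASS comparison and the sample size are untouched.

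**What to change.** Amend the Statistical analysis section in three places:

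1. Add EQ-5D utility to the outcomes analysed by GEE: values at six weeks, three months and one year, preoperative utility as covariate, and an approach-by-visit term.
2. Report the between-approach difference with 95% CI at each of these visits as the generic quality-of-life result.
3. Keep QALYs for the economic evaluation, state their horizon, and report the QALY difference with its own bootstrap 95% CI beside the ICER. The planned 5000 iterations already produce it.

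The cost is one or two sentences plus a few more secondary comparisons (three visit contrasts and one QALY difference), which should be labelled as secondary. No new data, visits or patients are needed.

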### Sample size calculation

Escobar et al. [30] showed that 70% of patients achieved an acceptable symptom state (PASS) at three months following THA, which means they have a positive PASS. The hypothesis is that the anterior approach results in a larger proportion of patients with a positive PASS at three months following THA. A difference of 20% in the proportion of patients with a positive PASS between the anterior approach and the posterolateral approach is considered clinically significant, as is described is described in the OMERACT-OARSI criteria [50]. Hence, based on the results of Escobar et al., a sample size of 60 patients in each study subgroup is needed to detect this difference of 20%, with a power of 80% and an alpha of 5%. Hence, each arm of the RCT needs to contain 120 patients. Based on previous experience, it is expected that approximately 10% will be lost in the follow-up. Hence, the total sample size will be set at 260 patients.

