There is still an ongoing debate within the orthopaedic community about the direct anterior approach for THA. This is partly due to the lack of well-designed prospective, randomized trials comparing the direct anterior with the most commonly used posterolateral approach. Moreover, there is a lack of literature about the cost-effectiveness of this tissue-sparing approach for THA. Therefore, the aim of this article is to compare the (cost-) effectiveness of the direct anterior approach with the posterolateral approach, with the hypothesis that the direct anterior approach will lead to faster recovery and a decrease in costs.

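### The bootstrap mean ICER and its 95% CI are an unreliable summary of uncertainty when the effect difference is within about 2 to 3 standard errors of zero

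*Protocol article*

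**What the plan says.** The last paragraph of Statistical analysis in the protocol article sets out the economic analysis in two steps.

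- **Point estimate.** Mean costs, mean effects (HOOS) and mean QALYs (EQ-5D) are calculated per arm, and the ICER is obtained "by dividing the difference in costs by the difference in effects/QALYs between the study and control group".
- **Uncertainty.** "Uncertainty surrounding the calculated ICER will be examined by the bootstrap method". An ICER is calculated in each of 5000 iterations, "which then will be combined to form a mean ICER with corresponding 95% CI".

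Two other statements bear on where the result may fall. Measurements expects the advantage of the anterior approach "mainly in the early recovery period". The Discussion gives the hypothesis that "the direct anterior approach will lead to faster recovery and a decrease in costs".

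**The concern.** The natural reading is that 5000 ratios are averaged and an interval is formed from them. That raises three difficulties.

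- **No stable mean.** If the bootstrap effect difference can come close to zero, a few replicates with tiny denominators dominate the average.
- **Ambiguous sign.** A saving of EUR 500 with a gain of 0.02 QALY gives -25,000, and so does an extra cost of EUR 500 with a loss of 0.02 QALY. The first is cheaper and better, the second dearer and worse. Positive ratios have the same ambiguity.
- **No ordering in the hypothesised quadrant.** With a saving of EUR 1,000, a gain of 0.02 gives -50,000 and a gain of 0.04 gives -25,000. The better result has the ratio closer to zero, so ranking ratios to form an interval does not rank outcomes.

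Cost-effectiveness is part of the trial's stated aim, and this is the only measure of its uncertainty that the article specifies.

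**Working it through.** The article states no ICER, cost variance or QALY variance, so there is no figure of its own to reproduce. All cost, QALY and threshold inputs below are assumptions.

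**1. Is a QALY difference near zero plausible?**

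- The sample size section says that "the total sample size will be set at 260 patients", with about 10% loss: 260 × 0.9 / 2 = 117 evaluable per arm.
- Standard error of the QALY difference = SD × √(2/117). For assumed SDs of 0.10, 0.15 and 0.20 this is 0.013, 0.020 and 0.026.
- An assumed utility gain of 0.10 lasting six weeks to three months gives 0.10 × 6/52 = 0.012 to 0.10 × 0.25 = 0.025 QALY.

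Under these assumptions the expected difference is about the size of its standard error. The expected share of replicates with a negative QALY difference is Φ(-difference/SE). For a difference of 0.02 it is 6%, 15% and 22% at the three SDs. For 0.05 it is 0.01%, 0.5% and 2.8%.

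**2. How does the averaged ICER behave?**

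Independent normal draws: QALY SE 0.02, cost difference EUR -300, cost SE 600, 5000 draws per run, 20 runs.

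| QALY difference | Distance from zero | Expected negative denominators in 5000 | Point ICER | Range of the mean ICER over 20 runs |
|---|---|---|---|---|
| 0.02 | 1 SE | 0.159 × 5000 ≈ 793 | -15,000 | -185,000 to +408,000 |
| 0.04 | 2 SE | 0.0228 × 5000 ≈ 114 | -7,500 | -93,000 to +44,000 |
| 0.06 | 3 SE | 0.00135 × 5000 ≈ 7 | -5,000 | -6,800 to -3,700 |
| 0.08 | 4 SE | 0.00003 × 5000 ≈ 0.2 | -3,750 | -4,200 to -3,800 |

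The mean was positive in 11 of 20 runs at 1 SE and in 3 of 20 at 2 SE, although the point ICER is negative. The exact limits depend on the seeds, which is itself the symptom.

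**3. What do the same inputs give on net benefit?**

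Incremental net benefit at threshold λ is λ × (QALY difference) - (cost difference), with SE √((λ × 0.02)² + 600²).

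- Difference 0.02, λ = 20,000: 400 + 300 = 700, SE 721, z = 0.97, probability cost-effective 83%.
- Difference 0.02, λ = 80,000: 1,600 + 300 = 1,900, SE 1,709, z = 1.11, probability 87%.
- Difference 0.04: z = 1,100/721 = 1.53 and 3,500/1,709 = 2.05, probabilities about 94% and 98%.

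**4. Does it also occur when patients are resampled?**

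One simulated dataset per scenario: 117 per arm, QALY SD 0.15, cost SD 4,000, correlation -0.2, cost difference -500. Each was bootstrapped with 20 seeds.

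- Difference 0.02 (point -25,000): mean ICER from -182,050 to +659,055; percentile interval about -255,000 to +207,000. Net benefit at 20,000 per QALY was 899 (95% interval -385 to 2,155), probability cost-effective 0.91.
- Difference 0.05 (point -10,000): -22,041 to -9,004.
- Difference 0.08 (point -6,250): -6,484 to -6,121.

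Both checks agree: unstable close to zero, stable at about 4 SE.

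**The case against.** The strongest reply is that little of the economic analysis is at risk. The point ICER is already the ratio of mean differences, the two differences show its quadrant, and the bootstrap is used only for uncertainty. That stands. A reader might infer that the whole cost-effectiveness result would be uninterpretable. The article does not support this, because only the bootstrap mean and its interval are affected.

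A second reply is that a clear effect removes the problem. This is largely right. The mean had the correct sign in all 20 normal-draw runs at 3 SE and was stable at 4 SE. A reader might infer that the rule misleads however clear the data are, and that is not so. At 2 SE, however, the mean was still positive in 3 of 20 runs while the probability of cost-effectiveness was 94% to 98%. A pre-specified method should not depend on a large difference being found.

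Third, every cost and QALY figure here is assumed, and nothing was calculated for the HOOS-based ICER. Both points stand. The HOOS ratio is exposed in the same way only if its difference is also close to zero relative to its standard error.

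Finally, an article may leave a cost-effectiveness plane or acceptability curve to a fuller plan, so their absence is no fault. The fault lies in the averaging rule that the article does state.

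**Conclusion.** The concern holds, limited to the bootstrap mean ICER and its 95% CI and conditional on the effect difference lying within about 2 to 3 standard errors of zero. In that range the mean can take the wrong sign, and the interval pools replicates with opposite meanings. Even with few sign changes in the denominator, the size of a negative ICER has no ordering in the cheaper-and-better quadrant that the trial hypothesises.

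The condition is plausible because benefit is expected mainly early, but the documents do not establish it. The numerical size rests on assumed SDs, costs and thresholds. The point ICER, the PASS analysis and the sample size are unaffected. This should be fixed in the economic analysis; it does not threaten the primary result.

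**What to change.** In the last paragraph of Statistical analysis:

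- Keep the point ICER as it stands, reported with the cost and effect differences that form it.
- Delete the averaged bootstrap ICER and its 95% CI.
- Keep the 5000 bootstrap samples, and from each retain the joint pair of cost difference and effect difference, for QALYs and likewise for HOOS.
- From those pairs report the cost-effectiveness plane with the share in each quadrant, an acceptability curve, and incremental net monetary benefit with a 95% CI at thresholds stated in advance.

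The cost is a change of wording and of output. No new data, patients or visits are needed, and the same bootstrap samples are used.
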